### Timeline of the intervention and measures

The 14-week HFPM program will be delivered in two cohorts (cohort 1: academic year 2023–2024; cohort 2: academic year 2024–2025) in four phases between February 2024 and May 2025 for both cohorts. The T0 baseline measurements for both cohorts will take place from October 2023 (cohort 1) and from October 2024 (cohort 2), followed by T1 measurements (from February 2024 for cohort 1 and from December 2024 for cohort 2), T2 measurements (from April 2024 for cohort 1 and from February 2025 for cohort 2), T3 measurements (from June 2024 for cohort 1 and from April 2025 for Cohort 2), T4 post-intervention measurements (from September 2024 for cohort 1 and from July 2025 for cohort 2), and a 1-year long-term follow-up measurement (T5) from July 2025 to 2026 (see Fig. 1).

**Fig. 1 Fig1:**
[figure not shown]
Timeline of the intervention and measure

### Setting

The study will take place at secondary schools of Koers VO (Rotterdam, the Netherlands).

These schools will be broadly representative of Dutch secondary schools with respect to the type of school (urban/rural, large/small and high/middle/low SES of the school).

### Recruitment

School recruitment will be conducted and finalized in the academic years 2023/2024 and 2024/2025 and started in December 2022 with a presentation about the study and the prevention program by the Principal Investigator (PI) for mental health professionals across the 82 secondary Koers VO schools (i.e., a collaborative school network). When schools consent to participate, the teacher-mentors will inform parents/main caregivers via email about school participation in the study and upcoming study procedures, such as the classroom presentations and the informed consent procedures.

Schools who express their interest in the trial will be visited between May 2023 and September 2024 by two trained PhD students. When schools consent to participate, all girls of grades 8 and 9 for both cohorts will be visited between August 2023 and December 2024 by the PhD students or trained research assistants for classroom presentations about the aim of the study, the screening procedure, the HFPM training program, the randomization procedure, and the measures and will be provided the opportunity to ask questions. The classroom meetings are informative, they are not mandatory. The teacher-mentors will inform the girls in advance that a class meeting is planned at which the PhD student or the trained research assistants will present information about the study. Girls can indicate to the teacher-mentors in advance if they do not want to be present at the classroom meeting and this choice is accepted without having to give a reason for non-participation. In the classroom meeting, girls will be explained that they are allowed to participate when we receive the informed consent forms of both girls of a dyad and the parents/caregivers of both dyads, and that it will be possible to form a dyad with a girl of another 8th or 9th grade class within the same school. Participation in more than one dyad will not be allowed. Girls will also not be allowed to form dyads during the classroom visits, and it will be explained that the teacher-mentor will be available for support when the girls experience challenges during dyad formation.

After the classroom visits, the teacher-mentors of all 8th and 9th grade classes will send information letters and digital informed consent forms to all girls and their parents/ main caretakers via email (send by teacher-mentors), with a gentle reminder after 2 weeks (email send by teacher-mentors). When there is no response from the girls, or when they explicitly choose not to participate, this choice is accepted without further inquiry. Parents/main caretakers of incomplete dyads will be contacted by telephone by the PhD students and the research assistants and will receive a reminder-telephone call after 2 weeks. All researchers who will obtain informed consent are having a recent BROK certificate (i.e., Basic course on Regulations and Organisation for clinical investigators).

To be eligible for inclusion, at least one of the two girls of one friendship dyad, or both girls, should have a score of at least one standard deviation above the mean co-rumination screening score on the Co-rumination Questionnaire-Short [21].

### Sample screening and cRCT

We will include 160 high-risk friendship dyads who are primarily characterized by high levels of co-rumination within their daily interaction patterns. “High risk” is defined on the dyadic level and implies that at least one of the two girls of one friendship dyad, or both girls, should have a score of at least one standard deviation above the mean co-rumination screening score (see below). Therefore, approximately 1000 girls of approximately 100 8th and 9th classes of Koers VO schools with written informed consent will be screened on maladaptive co-rumination through the Co-rumination Questionnaire-Short [21]. All girls will receive an email with a secured link to the online questionnaire and a request to complete the questionnaire within 1 week. A first reminder will be sent after 1 week, a second reminder after 2 weeks and finally, the research team will contact the girls by phone with a final prompt to complete the questionnaire.

After completing the screening procedure, all dyads with at least one of the two girls with a score of at least one standard deviation above the overall mean co-rumination screening score will be eligible for inclusion in the cRCT. Finally, 160 Dutch girls from age 13 to 15 years old with high levels of maladaptive co-rumination and their good or best friend from age 13 to 15 years old within the same secondary school (*n* = 320 girls; 160 dyads) will be included in the cRCT. In anticipation of 20% dropout, 16 dyads will be placed on a waiting list.

### In- and exclusion criteria

To be eligible for inclusion, a *participant/girl* must meet the following five inclusion criteria:Aged 13 to age 15 years.Visiting a secondary school of Koers VO (i.e., collaborative school network).Attending 8th or 9th grade of mainstream secondary education in academic year 2023/2024 or 2024/2025.Being a cisgender woman or being a transgender woman.Having a good or best friend (*being a cisgender woman or being a transgender woman) at the same school.

To be eligible for inclusion, a *dyad/girls* must meet the following inclusion criteria:By lack of an official cut-off score for high co-rumination levels, we will base our inclusion on a distribution-based technique. That is, we will include friendship dyads of which at least one of the two girls, or both girls, have a score of at least one standard deviation above the mean co-rumination screening score on the Co-rumination Questionnaire-Short [21]. This will result in a sample of the 16% highest scoring girls on co-rumination. Note that a distribution-based technique is a common-used technique to select a high-risk population of clinical significance in the absence of meaningful clinical cut-offs [61].

Exclusion criteria at the *school* level (to mitigate any risk of difficulties in trial implementation):Not having a headteacher in academic year 2023/2024 or 2024/2025.Judged as “inadequate” during the most recent school inspection by the Dutch Inspectorate of Education.Implementing another mindfulness-based intervention in academic year 2023/2024 or 2024/2025.

Exclusion criterium at the *individual* level:Following and/or participating in an individual or group-based mindfulness-based training in academic year 2023/2024 or 2024/2025.

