### Randomization, blinding, and treatment allocation

#### Sequence generation

Girls will be randomly assigned in a 1:1 ratio to the intervention group (80 dyads; *n* = 160 girls) or to the control group (CAU; 80 dyads; *n* = 160 girls) by an independent researcher, using CASTOR Electronic Data Capture (EDC), a web-based electronic case record form and randomization program that is compatible with the GCP guidelines.

Ideally, randomization takes place on 1 day, after the screening phase has been completed. However, when this is not possible (e.g., due to time limitations), we will follow the following procedure:

We will randomize dyads in batches of 50 dyads (100 girls). For the first batch, the mean and standard deviation (*SD*) will be computed and dyads in which one or both girls score 1 *SD* above the mean will be included in the study and randomly assigned to the treatment or control condition via a block randomization procedure (i.e., 50% of dyads assigned to the intervention arm and 50% assigned to the control arm). Next, the next 50 dyads (batch 2) will be screened, and a new mean and *SD* will be calculated for the group in total (i.e., 100 dyads). Then, dyads of batch 2 who adhere to the inclusion criteria are included and randomly assigned to the control or intervention condition. We proceed with this process until 1000 girls are screened and 160 dyads are included in the study.

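### Screening about 1000 girls is expected to give about 127 to 146 eligible dyads, not 160 (or 176 with the waiting list), and the enrolled sample is not the top 16% of girls

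*Protocol article*

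**What the plan says.** All of the following is in the protocol article.

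- **Screening volume** (Sample screening and cRCT): "approximately 1000 girls of approximately 100 8th and 9th classes of Koers VO schools with written informed consent will be screened".
- **Dyads are disjoint pairs.** Recruitment states: "Participation in more than one dyad will not be allowed". Sequence generation equates dyads and girls two to one: "We will randomize dyads in batches of 50 dyads (100 girls").
- **Eligibility** (In- and exclusion criteria, repeated in Recruitment): dyads qualify when "at least one of the two girls, or both girls, have a score of at least one standard deviation above the mean" screening score.
- **Claimed result of that rule** (In- and exclusion criteria): "This will result in a sample of the 16% highest scoring girls on co-rumination".
- **Expected sample** (Sample screening and cRCT): "160 Dutch girls from age 13 to 15 years old with high levels of maladaptive co-rumination and their good or best friend", which the section counts as 160 dyads and 320 girls. It adds 16 waiting-list dyads, and Withdrawal of individual subjects relies on these to replace dropouts.
- **End of screening under the batch procedure** (Sequence generation): "We proceed with this process until 1000 girls are screened and 160 dyads are included in the study".
- **Sample size calculation**: 80 dyads are required for d = 0.50 with ICC 0.20. The 160 is a maximum, reached by oversampling so that d = 0.35 can be detected and mediators and moderators studied.

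**The concern.** Sixteen per cent of 1000 is 160 girls, and the protocol appears to carry that number over as 160 dyads. The two counts agree only if no eligible dyad contains two high scorers, yet the rule expressly allows both girls to be high. Each such dyad uses up two high scorers and yields one dyad.

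Two things are at stake. The screening effort may be too small for the planned enrolment and for the replacement dyads, which erodes the oversampling meant for smaller effects. The description of the enrolled population is also wrong for a large share of participants, because the friend need not reach the cut-off.

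**Working it through.** **Inputs from the protocol:** 1000 girls, 500 dyads, cut-off at mean + 1 SD, 16% of girls above it (normal upper tail p = 1 − Φ(1) = 0.1587), target 160 dyads, waiting list 16, so 176 in total.

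**Assumptions:** the screening score is normal, all 1000 girls are in complete dyads, and the within-dyad correlation r of the screening score lies between 0 and 0.5. The protocol does not give r; its 0.20 concerns depressive feelings. A positive r is plausible because both friends rate their shared conversations about problems.

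**Step 1. Reproduce the 160.** With exactly one high scorer in every eligible dyad, the yield is 1000 × 0.16 = 160 (1000 × 0.1587 = 158.7). This is the only pairing that gives 160, and it is also the most that can be expected at 16%.

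**Step 2. Apply the one-or-both rule with independent friends.** The share of eligible dyads is 1 − (1 − 0.1587)² = 0.2921, and 500 × 0.2921 = 146. Using the rounded 16% gives 500 × (1 − 0.84²) = 147. About 500 × 0.1587² = 12.6 dyads hold two high scorers, and 158.7 − 12.6 = 146.1.

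**Step 3. Allow for correlation.** The share is q = 1 − Φ₂(1, 1; r), with Φ₂ the bivariate normal distribution function. Expected dyads are 500q. The chance of reaching a target is a binomial tail with 500 dyads. Girls to screen are 2 × target / q. The share of enrolled girls at or above the cut-off is p / q.

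| r | q | Expected dyads | Chance of ≥160 | Chance of ≥176 | Girls for 160 | Girls for 176 | High scorers among enrolled |
|---|---|---|---|---|---|---|---|
| 0 | 0.2921 | 146 | 9.4% | 0.2% | 1,096 | 1,205 | 54% |
| 0.2 | 0.2792 | 140 | 2.5% | 0.02% | 1,146 | 1,261 | 57% |
| 0.3 | 0.2719 | 136 | 1.0% | 0.005% | 1,178 | 1,295 | 58% |
| 0.5 | 0.2548 | 127 | 0.06% | <0.01% | 1,256 | 1,382 | 62% |

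**Step 4. Composition.** On the protocol's own count, 160 high scorers plus 160 friends is 50% high scorers, and 320 of 1000 is 32% of the screened girls. With the table, the range is 50% to 62%. Under none of these readings is the sample the top 16%.

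**Step 5. Consequence for precision.** I assume a two-sided 5% level, which the article does not state, and use its ICC of 0.20. With two girls per dyad the design effect is 1 + 0.20 = 1.2. For D dyads in total, the effective number per arm is D / 1.2. The detectable d at 80% power is (1.96 + 0.84) × √(2 / (D / 1.2)), and power for d = 0.35 is Φ(0.35 / √(2 / (D / 1.2)) − 1.96).

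| Dyads | Effective n per arm | Detectable d | Power for d = 0.35 |
|---|---|---|---|
| 160 | 133.3 | 0.34 | 82% |
| 146 | 121.7 | 0.36 | 78% |
| 127 | 105.8 | 0.39 | 72% |

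These are normal approximations, before any dropout.

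**The case against.** A reader might infer that 1000 girls cannot yield 160 dyads, or that 146 is a maximum. The documents do not support that. The 146 is an expectation under normality and independence, with about a 9% chance of 160 or more. At exactly 16%, the expected yield could be as high as about 160 if no two high scorers were paired. The figure of 1000 is itself approximate. The screening score is a five-item scale rated 0 to 4, so the share above mean + 1 SD need not be 16%. A share of about 17.5% would give 160 dyads under independence, and about 18.5% would do so at r = 0.2.

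A reader might also infer that the batch procedure contradicts itself by asking for both 1000 screened and 160 included. The wording can equally mean that screening continues until both hold, and it belongs to a fallback used only if randomization on one day is not possible. On that reading there is no contradiction, but 1000 is then too low as a planning figure.

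On importance, the protocol requires 80 dyads. Yields of 127 to 146 exceed that by 59% to 82%, and no bias in the analysis follows. The 16% sentence comes directly after a correct statement of the dyad rule, so eligibility is unlikely to be misapplied.

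These points limit the strength and severity of the finding. They do not remove it: on the protocol's own figures the expected yield is below 160, 176 is out of realistic reach, and the 16% sentence is inaccurate for the enrolled sample.

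**Conclusion.** The point holds in moderate form. From 1000 girls in complete dyads, with 16% above the cut-off, about 146 eligible dyads are expected if friends' scores are independent and about 140 to 127 at correlations of 0.2 to 0.5. That is about 14 to 33 short of 160 and 30 to 49 short of 176. The correlation and the normal shape are assumptions. Incomplete dyads would lower the yield, and a different share above the cut-off would move it either way.

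The population statement is wrong without any distributional assumption, because the rule enrols friends regardless of their own score. About 50% to 62% of enrolled girls would be high scorers.

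The comparison for d = 0.50 keeps its stated size. What weakens is the margin for d = 0.35 and for the mediation and moderation questions, with a detectable d of about 0.36 to 0.39 in place of 0.35.

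**What to change.** 1. Restate the screening yield in one of two ways:
   - keep 160 dyads and plan for about 1,100 to 1,260 girls in complete dyads, or about 1,200 to 1,380 to fill the waiting list as well, stating the assumed within-dyad correlation; or
   - keep 1000 girls and restate expected enrolment as about 127 to 146 dyads, with a detectable d of about 0.36 to 0.39 at 80% power (two-sided 5%, ICC 0.20).
2. In Sequence generation, say whether screening continues past 1000 girls if 160 dyads have not been reached.
3. In In- and exclusion criteria, let the 16% refer to screened girls at or above the cut-off, and describe the sample as dyads with at least one such girl.

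The cost is restated figures and one reworded sentence. If 160 dyads are kept, there is also some extra online screening: roughly 100 to 260 more girls, or 200 to 380 more with the waiting list. The observed share above the cut-off and the within-dyad correlation in the first screening batch would show where in these ranges the trial lies.

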### Randomization, blinding, and treatment allocation

#### Sequence generation

Girls will be randomly assigned in a 1:1 ratio to the intervention group (80 dyads; *n* = 160 girls) or to the control group (CAU; 80 dyads; *n* = 160 girls) by an independent researcher, using CASTOR Electronic Data Capture (EDC), a web-based electronic case record form and randomization program that is compatible with the GCP guidelines.

Ideally, randomization takes place on 1 day, after the screening phase has been completed. However, when this is not possible (e.g., due to time limitations), we will follow the following procedure:

We will randomize dyads in batches of 50 dyads (100 girls). For the first batch, the mean and standard deviation (*SD*) will be computed and dyads in which one or both girls score 1 *SD* above the mean will be included in the study and randomly assigned to the treatment or control condition via a block randomization procedure (i.e., 50% of dyads assigned to the intervention arm and 50% assigned to the control arm). Next, the next 50 dyads (batch 2) will be screened, and a new mean and *SD* will be calculated for the group in total (i.e., 100 dyads). Then, dyads of batch 2 who adhere to the inclusion criteria are included and randomly assigned to the control or intervention condition. We proceed with this process until 1000 girls are screened and 160 dyads are included in the study.

#### Concealment mechanism

Intervention allocation will be concealed by using a web-based application with a computer-generated list that will not be disclosed. Participants and researchers are aware of allocation.

#### Implementation

After obtaining informed consent, dyads will be randomly allocated to one of the two intervention arms by the independent researcher using Castor EDC.

### Assignment of intervention: blinding

#### Who will be blinded

Due to the organizational structure of the prevention program, students, parents, school, and research staff will not be blind to treatment allocation.

#### Procedure for unblinding if needed

The trial design is open label so unblinding will not occur.

### Sample size calculation

Multi-level models are used with individuals nested in dyads. With a clinical relevant effect size, that is, a difference of 1 *SD* (i.e., Cohen’s *d* = 1) between the control and intervention group where high-risk girls (*M* + 1 *SD*) score on average similar to non-high-risk girls on co-rumination (*M*) after the intervention, and a small to moderate effect association between co-rumination and internalizing problems (Cohen’s *d* = 0.50; [15]), which will result in a possible reduction of depressive feelings with 0.50 *SD*, and an ICC of depressive feelings within dyads of 0.20, 80 dyads (40 control, 40 intervention) will be required (Optimal Design; [62]). However, we will aim to oversample to a maximum of 160 dyads in order to identify smaller effects (Cohen’s *d* = 0.35) that are potentially relevant for theory development, as well as our hypothesized mediating and moderating factors as described in the “Data analysis plan” section.

### HFPM app-based mindfulness training program

The HFPM school-based mindfulness prevention program [57, 58] aims to teach emotion regulation and mindfulness skills on *the dyadic level* that support resilience and the positive qualities of girls’ dyadic friendships with the aim to prevent excessive co-rumination and (early onset of) internalizing symptoms (e.g., depression, anxiety). Mindfulness will be operationalized within this program as a natural and trainable capacity to bring *awareness* to both inner (e.g., body sensations, feelings, thoughts) and outer (e.g., friendships, stressors) experiences with qualities of attention, kindness, curiosity, and responsiveness, without judgment and with being in the present moment in a sustained and intentional way [41].

The App yourself Happy app for excessive co-ruminating early adolescent female friendship dyads [58] is the backbone of the prevention program and primarily aimed at supporting girls getting out of “the autopilot of negative reactivity.” Daily working with the app is supported by 14 manualized weekly online training sessions via Teams (30–50 min each; during school hours, i.e., mentor or free homework hours; girls will receive Teams-meeting links via email), aimed to teach girls to implement the mindfulness-based principles of the app in their daily lives and throughout their friendship activities and interactions. The app and the mindfulness sessions will be using an integrative combination of behavioral activation, mood monitoring, journaling, short guided and dyadic meditation practices, and homework practices. Girls who do not have their own smartphone will borrow one from Rotterdam University of Applied Sciences.

In order to teach and stimulate girls to discover new healthy and positive shared alternatives for excessive co-rumination and rumination (getting out of autopilot negative reactivity), to stimulate present-moment awareness and appreciation of pleasant shared experiences and interactions, to encourage girls to share their interpersonal responses to pleasant experiences and positive affect with each other, to teach girls to work skillfully with difficult emotions during activities and interactions and to support friendship dyads to incorporate these healthy alternatives in their daily lives, dyadic-friendship girls will participate and will be supported together by the training program and encouraged to use the App yourself happy module “Healthy, joyful dyadic activities” on a daily basis. This module contains 150 healthy and joyful behavioral activation activities for dyadic use with the following categories: Beauty, On the road, Creative, Educative, Game time, Indoor, Outdoor, Mindfulness, Sport, Relax, and Kitchen. Each activity is presented on a photocard with fun and inspiring tips about the preparation of the activity and information about the costs and other important aspects (e.g., “for this activity you need a towel”). Girls will be able to select five activities and share these with their dyad friend via a WhatsApp message.

Friendship dyads will be encouraged in the weekly training sessions to do at least one or two activities each week. These behavioral activities (including the preparations and the reflections on the activities through journaling and reflections during the weekly training sessions) will function as a natural backbone to train several mindfulness skills: being in the present moment (present-moment awareness), conducting random acts of kindness, experiencing joy and gratitude using the ten fingers gratitude practice, using the pleasant experiences calendar and creating more nurturing experiences, and using the unpleasant experiences calendar and diminishing the impact of depleting experiences. In every training session, a new mindfulness practice will be introduced by connecting practice with upcoming activities and skills practicing. The use of these practices will be stimulated by several animation videos with explanations about co-rumination, brain functioning on automatic pilot, and a guided mediation practice. Working with mindfulness skills and practices during the activities and within daily live interactions will be evaluated and reflected on during the online training sessions, and girls will be encouraged and trained to incorporate these mindfulness practices within other and new activities in their daily interactions.

This continuous process of training, reflection, and integration in daily live will be supported by using the journaling module of the app, with daily journaling guided by randomly selected positively formulated mindfulness-based questions (morning, afternoon, and evening), aimed at practicing gratitude and optimism related to (a) daily experiences (always) and (b) positive anticipation on upcoming shared activities and (c) recalling positive memories after completing an activity (during activity planning and after completing activities). This module encourages girls three times a day to actively report on the positive aspects of preparing the activities together with their dyad friend, to actively recall positive memories about the activity as well as aspects of the friendship/sharing and the mindfulness practices after completing an activity. They will be encouraged to share their positive thoughts and positive emotions within their daily journaling and daily interactions and conversations.

During the training sessions, girls will be invited to share their experiences about their cultivated adaptive awareness of together dwelling on negative emotions and the impact of their training practices on awareness of sharing and responding on positive affect. This process will be specifically supported by using the mood tracker and calendar, facilitating girls to reflect on practicing mindfulness-based activities and their daily emotions.

Daily state mood monitoring possibilities (three times a day: morning, afternoon, and evening) are Positive Affect (PA): Cheerful (high arousal), Content (low arousal), Happy (high arousal), Energetic (high arousal), Relaxed (low arousal), and Joyful (high arousal) and Negative Affect (NA): Worried (high arousal), Anxious (high arousal), Low/Depressed (low arousal), Insecure (low arousal), Irritated (high arousal), and Guilty (low arousal). Girls will be asked to report one PA and/or one NA on a 5-point scale, ranging from 0 (*not at all*) to 4 (*very much*). The PA and NA items were derived from work of Barrantes-Vidal and colleagues [62]. A monthly overview of the experienced moods and their intensity will be available within the Mood calendar. Girls will receive daily empathetically formulated prompts on pre-programmed moments (indicated by the girls themselves) for using the mood monitoring, journalling, and diary function of the app and daily rewards (i.e., psychoeducation), offered at completing daily mood monitoring and journaling. This is embedded to boost engagement with the app on a daily basis. It is hypothesized that actively practicing these skills and reflecting on the impact on their emotions and thoughts will explicitly target repetitive negative, judgmental emotions and thoughts in the interactions and communication of the participating girls. Girls will spend a total of no more than 15 min a day completing the mood tracker and diary.

